#### Staging laparoscopy

SL will be performed after the PET, prior to the initiation of treatment, and should be performed by or under supervision of a gastrointestinal or oncological surgeon. During staging laparoscopy, the goals are to evaluate the resectability of the primary tumor (T-stage) and to evaluate the presence or absence of peritoneal metastases. To evaluate the resectability of the tumor, a thorough inspection of the region of the stomach and tumor along with surrounding organs will be performed. In case of a tumor localized at the posterior wall of the stomach, it is advised to open the omental bursa and inspect it accordingly. To evaluate the presence or absence of peritoneal metastases, all quadrants of the peritoneal cavity and Douglas’ pouch will be inspected. In case of suspicious macroscopic lesions, biopsies will be taken and sent for histological review. When macroscopic lesions are present, all thirteen regions of the abdomen will be evaluated and the peritoneal cancer index (PCI) will be scored [17]. Cytology of the peritoneal cavity should be performed (500cm^3^ dispersed throughout all quadrants and Douglas’ pouch) as it is a promising prognostic factor with possible implications for treatment in the future [18, 19].

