## Background

Gastric cancer is the fifth most common type of cancer worldwide [1]. In Western countries, curative treatment consists of gastrectomy with perioperative chemotherapy [2–4]. Unfortunately, the prognosis of patients who undergo curative treatment remains relatively poor, with a 5-year overall survival rate of 20–40%. The main cause for this poor prognosis is tumor recurrence [2, 5]*.* The poor prognosis, treatment-related morbidity and mortality, and impairments in quality of life result in a high disease burden [6].

The standard diagnostic work-up of patients with gastric cancer includes a gastroscopy to assess tumor size and location and to obtain tissue to characterize the tumor. Furthermore, computed tomography (CT) of the thorax and abdomen is performed to detect metastases and evaluate local resectability. However, the accuracy of CT for detecting metastatic disease (M1) or local irresectability (T4b) is low: the sensitivity to detect peritoneal metastases is 22%–33%, to detect distant metastases is 14%–65% and to detect T4b disease is 5%–69% [7–10]. Consequently, two undesirable situations may occur in practice:

1. Unexpected intraoperative peritoneal metastases or local tumor irresectability are found at the onset of gastrectomy.

2. Undetected distant metastases presenting shortly after treatment with curative intent (neoadjuvant chemotherapy and/or surgery).

In both situations, patients undergo a futile treatment, probably leading to a reduced quality of life and an increase in health care costs.

A recent study from the United States investigated the additional staging capacities of fluorodeoxyglucose positron emission tomography with CT (PET) and staging laparoscopy (SL) in gastric cancer. In this study, combination of PET and SL identified additional metastases in 27% of patients: distant metastases by PET in 10% of patients, and peritoneal metastases by SL in 19% of patients (with an overlap of 2%) [11]*.*To reduce the number of patients undergoing futile treatment, the new Dutch guidelines for the treatment of gastric cancer recently included PET and SL in the staging algorithm of locally advanced (cT3–4) tumors“(http://www.oncoline.nl/maagcarcinoom)”. However, this guideline concludes that the evidence for both staging modalities is weak, and additional studies are needed to further investigate the cost-effectiveness and applicability of routinely adding PET and SL to the staging of locally advanced gastric cancer.

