## Methods

### Objectives

The primary outcome of this study is the proportion of patients in whom PET and SL lead to a change in treatment strategy. The accuracy of each modality will be analyzed separately. Secondary outcome parameters are diagnostic performance (sensitivity, specificity, positive and negative predictive value), morbidity and mortality, quality of life, cost reduction and cost-effectiveness. The hypothesis of this study is that adding PET and SL to additional staging in these patients will lead to a change of treatment strategy in 27% of patients, leading to an annual cost reduction in the Netherlands of €916.438 by reducing futile treatment.

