### Study population

The study population consists of patients with a surgically resectable, advanced gastric adenocarcinoma (cT3–4b, N0–3, M0), who are scheduled for treatment with curative intent after initial staging with gastroscopy and CT. Patients’ inclusion and exclusion criteria are defined as follows:

Inclusion criteria:

• Histologically proven adenocarcinoma of the stomach or esophagogastric junction (Siewert type III) as observed by gastroscopy.

• Underwent evaluation with CT of the abdomen and chest.

• Surgically resectable, advanced gastric cancer (cT3–4b, N0–3, M0), as determined by the multidisciplinary team (MDT).

• Intention to perform a potentially curative gastrectomy with or without perioperative treatment.

Exclusion criteria.

• Siewert type I-II esophagogastric junction tumor.

• Unfit or unwilling to undergo surgery.

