#### Treatment

If the tumor is deemed to be resectable, patients will be scheduled for treatment. Treatment will not be initiated before completion of staging according to the Dutch guidelines, including PET and SL [15]. There are no additional restrictions to the further treatment strategy, such as chemotherapy regimen or type/approach of resection.

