### Statistical analysis

The primary outcome measures, change in treatment strategy of PET and SL, will be presented as a percentage. To evaluate the performance of PET and SL, sensitivity and specificity will be calculated. A separate analysis will be performed to assess whether both diagnostic modalities are accurate for various subgroups, for instance tumor types (Lauren classification: diffuse, intestinal and mixed). The quality of life of patients in this study will be compared to previous data from literature and to a retrospective cohort of patients who did not undergo PET and SL. Differences are tested using linear mixed-effects modeling, taking relevant patient characteristics into account. Missing values will be imputed using multiple imputation techniques. Statistical significance is defined as *p* < 0.05. Cost-effectiveness will be calculated, taking all relevant health-related costs into account, including costs arising from complications of medical treatment, and additional diagnostics arising from false-positive findings on PET. A model (Fig. 2) will be developed to compare health care costs with only CT. A budget impact analysis (BIA) will be performed, adhering to the newest guidelines and applying the societal, health insurance/third party payer and health care perspectives. Analyses will be performed for the combination of PET and SL and for both treatment modalities separately.

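### Staging laparoscopy negatives are verified only after treatment has begun, usually after chemotherapy, so the planned sensitivity and NPV of SL for peritoneal metastases do not describe disease at the time of SL

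*Protocol article*

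**What the plan says.** **Timing.** Methods, Staging laparoscopy: "SL will be performed after the PET, prior to the initiation of treatment". Methods, Treatment: "Treatment will not be initiated before completion of staging according to the Dutch guidelines, including PET and SL".

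**Pathway after a negative SL.** Background: "In Western countries, curative treatment consists of gastrectomy with perioperative chemotherapy". Methods, Study population, also admits patients treated without it: "Intention to perform a potentially curative gastrectomy with or without perioperative treatment". The share of such patients is not given. Methods, Treatment, leaves the interval unstandardised: "There are no additional restrictions to the further treatment strategy, such as chemotherapy regimen or type/approach of resection".

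**Verification.** Under Staging laparoscopy, suspicious macroscopic lesions are biopsied for histology, so a positive SL is confirmed at the time. Peritoneal cytology should also be taken, but the article presents it as a prognostic factor, not as a check on SL. No pre-treatment check of a negative SL is described.

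**Planned measures.** Methods, Objectives: "Secondary outcome parameters are diagnostic performance (sensitivity, specificity, positive and negative predictive value". Methods, Statistical analysis: "To evaluate the performance of PET and SL, sensitivity and specificity will be calculated".

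**The concern.** Sensitivity and NPV describe how well a test classifies disease that is present when the test is done. Here the two arms of the 2×2 table are verified differently. SL-positive patients are classified at the laparoscopy. SL-negative patients are classified after an interval that contains at least the start of treatment and, on the usual pathway, chemotherapy.

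Two errors follow, and they pull in opposite directions:

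- Peritoneal disease that develops between SL and surgery is charged to SL as a miss. This lowers apparent sensitivity and NPV.
- Disease missed at SL that regresses under chemotherapy, or that is never inspected because the patient is not operated on, is credited to SL as a true negative. This raises both.

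The article intends its results for an updated national guideline. A figure labelled sensitivity or NPV would be read there as the accuracy of SL at staging, which for most SL-negative patients the data would not measure.

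**Working it through.** The article states no accuracy figure for SL in this study, so there is none to reproduce. The check has two parts.

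**1. Order of events**

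| Step | SL-positive | SL-negative |
|---|---|---|
| SL | before treatment | before treatment |
| Verification | biopsy at SL | gastrectomy or follow-up |
| Treatment between SL and verification | none | usually chemotherapy; none if gastrectomy comes first |

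Naming a reference standard would not close this gap. If the standard is the finding at gastrectomy, or follow-up, the interval remains.

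**2. Size, as an illustration**

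Inputs from Background (the cited US study): PET finds distant metastases in 10%, SL finds peritoneal metastases in 19%, overlap 2%. Because SL follows a PET without distant metastases, per 100 patients:

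- reaching SL: 100 − 10 = 90
- SL-positive: 19 − 2 = 17
- SL-negative: 90 − 17 = 73

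Assumptions, not in the documents: 3 true misses at SL, 0 to 4 new cases before surgery, 0 to 2 missed cases cleared by chemotherapy.

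Apparent misses = 3 − cleared + new. Apparent sensitivity = 17 / (17 + apparent misses). Apparent NPV = 1 − apparent misses / 73.

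| Scenario | Apparent misses | Sensitivity | NPV |
|---|---|---|---|
| 2 cleared, 0 new | 1 | 17/18 = 94.4% | 72/73 = 98.6% |
| Truth at SL | 3 | 17/20 = 85.0% | 70/73 = 95.9% |
| 0 cleared, 4 new | 7 | 17/24 = 70.8% | 66/73 = 90.4% |

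Now assume that 10% of SL-negative patients (7.3) are never operated on, and that the misses above are all found in operated patients. If every unoperated patient is counted as diseased, NPV is 1 − (3 + 7.3)/73 = 85.9%. With the 4 new cases added it is 1 − (7 + 7.3)/73 = 80.4%.

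**Second set of assumptions.** Take 239 × 0.90 ≈ 215 patients at SL, 19% of them SL-positive, all SL-negatives verified, new disease in 0 to 10% of true negatives, and 0 to 50% of missed disease cleared.

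| True sensitivity (true NPV) | Apparent sensitivity | Apparent NPV |
|---|---|---|
| 0.80 (0.941) | 0.61 to 0.89 | 0.85 to 0.97 |
| 0.90 (0.974) | 0.66 to 0.95 | 0.88 to 0.99 |

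With new disease in 5% of true negatives and no clearance, sensitivity falls from 0.80 to 0.69, or from 0.90 to 0.76.

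**The case against.** **The article never names gastrectomy findings as the reference standard for SL.** This is true. The full protocol or SAP may define a reference standard and a time window, and their absence from a condensed article is not the finding. What stands is that the fixed order of SL, treatment and verification, together with a commitment to report sensitivity and NPV, creates the problem whatever later standard is chosen.

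**Gastrectomy is not the only later look.** A reader might infer that SL misses can be seen only at gastrectomy and that unoperated patients are never observed again. The documents do not support that. The Time schedule provides follow-up, and missed disease may also surface during chemotherapy. These looks also come after treatment has begun, so the mixing remains. The Background sentence "Unexpected intraoperative peritoneal metastases or local tumor irresectability are found at the onset of gastrectomy" describes a consequence of inaccurate CT. It shows where unexpected disease comes to light but does not say how SL will be verified.

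**How many patients have chemotherapy first is not stated.** *Usually* rests on one general Background sentence, and surgery without perioperative treatment is allowed. This limits how firmly the affected share can be stated.

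**For residual futile surgery, the later finding is the right quantity.** This stands. Peritoneal disease found at gastrectomy after a negative SL, whether missed or new, answers that question directly. The objection is to calling it a false-negative rate or NPV of SL.

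**Restricting to upfront gastrectomy would solve it.** It would not solve it for sensitivity. SL-positive patients are largely those in whom curative surgery is prevented, so few enter that group. True positives approach zero, and 0/(0 + misses) is zero or undefined. Only NPV can be computed there, and the group is selected.

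**Conclusion.** The point holds for the sensitivity and NPV of SL for peritoneal metastases, and to a lesser degree for specificity through the true-negative count. These estimates would mix disease missed at SL, disease new since SL, and disease regressed or not inspected.

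The ranges shown (for instance 71% to 94% around a true sensitivity of 85%) rest on assumed numbers of misses, new cases, cleared cases and unoperated patients. They show that the distortion could matter, not that it will have that size. A reader might infer that SL accuracy will be overstated, or understated. The documents support neither, because the two errors oppose each other and the planned data do not separate them.

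Nor does the point reach the main result. The primary outcome counts changes in treatment strategy after PET or SL, and PPV rests on biopsy at SL. Neither depends on later verification of SL-negatives. This is an inexpensive improvement to a secondary analysis.

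**What to change.** In the analysis of SL performance for peritoneal metastases:

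1. Among SL-negative patients, report the proportion with peritoneal metastases at gastrectomy separately for those with and without preoperative chemotherapy, with the SL-to-surgery interval in each group.
2. Treat that proportion as 1 − NPV at the time of SL only in the group without preoperative chemotherapy, with a caveat that this group is selected.
3. In the chemotherapy group, label it *peritoneal metastases found at gastrectomy after a negative SL*, not a false-negative rate or 1 − NPV.
4. Describe any overall SL sensitivity as conditional on delayed verification. Do not restrict sensitivity to patients with upfront gastrectomy.
5. For SL-negative patients who are never operated on, give best- and worst-case bounds (none diseased, all diseased).

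**Cost.** The change is one stratification, wording and two bounds, with no change to patient care. It needs the dates of SL and surgery, preoperative chemotherapy given or not, and peritoneal findings at surgery. The article does not say whether these are recorded, so this should be confirmed. The NPV estimate without chemotherapy rests on fewer, selected patients and will have a wider interval.

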### Outcome measurements

The primary outcome of this study is the proportion of patients in whom PET and/or SL leads to a change in treatment strategy. This includes the proportion of patients in whom surgery with curative intent is prevented, and the proportion of patients in whom the chemotherapy regimen is changed or omitted. Secondary outcome parameters include cost-effectiveness, modality-specific performances (diagnostic performance of both modalities, incidental findings on PET), patients’ extra burden of the diagnostic modalities (morbidity and mortality, diagnostic delay, number of extra MDT’s held), and overall quality of life of patients (EORTC Quality of Life questionnaires).

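### Staging laparoscopy verdicts of local irresectability have no stated independent reference, so specificity, PPV and unbiased sensitivity for that target cannot be estimated; NPV in operated patients can

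*Protocol article*

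**What the plan says.** - **Objectives:** "Secondary outcome parameters are diagnostic performance (sensitivity, specificity, positive and negative predictive value" are listed, and "The accuracy of each modality will be analyzed separately". Outcome measurements repeats this as "modality-specific performances (diagnostic performance of both modalities, incidental findings on PET".
- **Statistical analysis:** "To evaluate the performance of PET and SL, sensitivity and specificity will be calculated". Predictive values are not mentioned again there.
- **Staging laparoscopy:** "the goals are to evaluate the resectability of the primary tumor (T-stage) and to evaluate the presence or absence of peritoneal metastases". For the first goal, "To evaluate the resectability of the tumor, a thorough inspection of the region of the stomach and tumor along with surrounding organs will be performed". Histology is described for suspicious macroscopic lesions, within the text on peritoneal disease.
- **Treatment:** patients are scheduled when the tumour has been judged resectable. No operative check is described for the others.
- **Use of T4b:** the Background states that "the accuracy of CT for detecting metastatic disease (M1) or local irresectability (T4b) is low", while Study population admits "Surgically resectable, advanced gastric cancer (cT3–4b, N0–3, M0), as determined by the multidisciplinary team (MDT".

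**The concern.** SL has two targets, and they differ in how a positive call can be checked. A suspected peritoneal lesion goes to histology, so a false positive can be seen. A tumour called irresectable is judged by eye, and that verdict takes the patient off the path to the gastrectomy that could have contradicted it. This is partial verification: who receives a reference result depends on the result of the test being evaluated.

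The risk is that specificity and PPV for irresectability appear perfect without having been tested. The Discussion says that the results will go into an updated national guideline. The Statistical analysis section mentions costs of false-positive findings for PET and names no counterpart for SL. The primary outcome, the proportion with a changed treatment strategy, does not use these accuracy parameters.

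**Working it through.** The article gives no figure for SL accuracy on resectability, so there is nothing to reproduce. The check has two parts.

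**1. Who has a reference result for irresectability**

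| SL verdict | Next step in the article | Reference available |
|---|---|---|
| Resectable | Scheduled for treatment | Finding at the start of gastrectomy (Background, first undesirable situation), if surgery is reached |
| Irresectable | Not scheduled on that path | None stated |

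Let TP and FP be the correct and wrong irresectable verdicts, and FN and TN the wrong and correct resectable verdicts. Only FN and TN can be told apart.

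- *Irresectable verdicts counted as true:* apparent PPV = (TP+FP)/(TP+FP) = 100%; apparent specificity = TN/TN = 100%; apparent sensitivity = (TP+FP)/(TP+FP+FN), which exceeds TP/(TP+FN) when FP > 0 and FN > 0.
- *Irresectable verdicts excluded:* PPV = 0/0, undefined; specificity = TN/TN = 100%; sensitivity = 0/FN = 0%.
- *Either way:* NPV = TN/(TN+FN), which uses SL-negative patients only and is unchanged.

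**2. Illustration of size**

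Inputs from the article: minimum sample 239 (Sample size calculation) and 10% with distant metastases on PET (Background). These give 239 × 0.90 ≈ 215 laparoscopies.

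Assumed, because the article gives no values: irresectability 5% or 10%, SL sensitivity 60% or 80%, SL specificity 95%, 99% or 100%. All SL-negative patients are taken to reach surgery.

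One row in full (5%, 60%, 95%):
- Irresectable: 215 × 0.05 = 10.75. TP = 10.75 × 0.60 = 6.45; FN = 4.30.
- Resectable: 204.25. FP = 204.25 × 0.05 = 10.21; TN = 194.04.
- True PPV = 6.45/16.66 = 38.7%, reported as 100%.
- Apparent sensitivity = 16.66/20.96 = 79.5%, true value 60%.
- NPV = 194.04/198.34 = 97.8%.

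| Irresectable | True sens. | True spec. | TP | FP | FN | TN | True PPV | Apparent sens. | NPV |
|---|---|---|---|---|---|---|---|---|---|
| 5% | 60% | 95% | 6.5 | 10.2 | 4.3 | 194.0 | 38.7% | 79.5% | 97.8% |
| 5% | 60% | 99% | 6.5 | 2.0 | 4.3 | 202.2 | 75.9% | 66.4% | 97.9% |
| 5% | 80% | 95% | 8.6 | 10.2 | 2.2 | 194.0 | 45.7% | 89.7% | 98.9% |
| 5% | 80% | 99% | 8.6 | 2.0 | 2.2 | 202.2 | 80.8% | 83.2% | 98.9% |
| 10% | 60% | 95% | 12.9 | 9.7 | 8.6 | 183.8 | 57.1% | 72.4% | 95.5% |
| 10% | 60% | 99% | 12.9 | 1.9 | 8.6 | 191.6 | 87.0% | 63.3% | 95.7% |
| 10% | 80% | 95% | 17.2 | 9.7 | 4.3 | 183.8 | 64.0% | 86.2% | 97.7% |
| 10% | 80% | 99% | 17.2 | 1.9 | 4.3 | 191.6 | 89.9% | 81.7% | 97.8% |

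At 100% specificity there are no false positives: PPV is truly 100% and sensitivity is unbiased. The study as described could not distinguish that case from the rows above.

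**The case against.** The strongest reply is that the article never says accuracy will be calculated for resectability. The sentence on SL describes the aims of a procedure, and the Statistical analysis section names only sensitivity and specificity. The first part is correct: the target is inferred from Objectives, Outcome measurements and Staging laparoscopy together. It is still the natural reading, because nothing limits SL accuracy to peritoneal disease.

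A second reply is that target and reference standard may be defined in a full protocol or analysis plan that is not shown. Their absence from an article is indeed no fault. But the gap here comes from the stated patient pathway, and a definition cannot supply an operative result for someone who was not operated on. The MDT section allows an extra modality and a third meeting, but only occasionally and not as a check on this verdict.

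Stronger readings are tempting and not supported:

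- *All predictive values are lost.* NPV is not; it needs only SL-negative patients who reach surgery.
- *T4b is contradictorily both irresectable and eligible.* Eligibility requires the stage and an MDT judgement of resectability together, and the Background use is shorthand. The wording is loose rather than fatal.
- *Resected pT4b tumours will lower SL sensitivity.* No section scores SL against pathological T4b, so that loss would rest on a rule the reader supplies.
- *A 100% value enters the decision tree.* The figure is not shown, so its inputs are unknown.
- *The problem extends to peritoneal metastases.* Biopsy gives SL-positive patients a reference there.

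**Conclusion.** The point holds for one of the two SL targets. On the pathway described, specificity and PPV for local irresectability are either 100% by construction or, for PPV, undefined. Sensitivity is either inflated or 0%.

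Under the assumed rates, a true PPV of 39–64% (specificity 95%) or 76–90% (99%) would be shown as 100%. A true sensitivity of 60% would appear as 63–80%, and one of 80% as 82–90%. NPV stays at 95.5–99.0% over the whole grid, including 100% specificity. In practice it carries caveats for patients who do not reach surgery and for change in the tumour during neoadjuvant treatment.

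The conclusion rests on two readings: that SL accuracy covers both stated goals, and that irresectable verdicts receive no routine independent check. The sizes are illustrative. This concerns a secondary outcome and should be corrected before the accuracy results are reported.

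**What to change.** Analyse the two SL targets separately.

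1. **Peritoneal metastases:** macroscopic impression as index test, biopsy histology as reference for SL-positive patients.
2. **Local irresectability:** define the target as irresectable at operation rather than T4b. Report the SL yield and the NPV among operated patients, with the number who did not reach surgery. State that specificity, PPV and unbiased sensitivity are not estimable.
3. **Cost-effectiveness model:** if it uses an accuracy value for SL irresectability, vary the false-positive share in a sensitivity analysis instead of entering 100%.
4. **Terminology:** reconcile the use of T4b, T-stage and irresectability across Background, Study population and Staging laparoscopy.

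The cost is wording and at most one sensitivity analysis, with no new data and no change to patient care. The downside is that some planned secondary parameters are reported as not estimable for this target.
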